Weight		X			X		X
Number of falls		X			X		X
Use of emergency services		X			X		X

*Abbreviations: CERAD* Consortium to Establish a Registry for Alzheimer’s Disease, *DBI* Drug Burden Index, *GDS* Geriatric Depression Scale, *NHPP* number of hospitalisations per patient, *PIM* potentially inappropriate medications, *SPIRIT* Standard Protocol Items: Recommendations for Interventional Trials, *TNM* total number of medications

Participant retention and complete follow-up will be promoted via phone calls by the study nurses. For patients who drop out of the study, the following parameters are requested by the GPs: hospitalisations, cardiovascular events (e.g., stroke, myocardial infarction), mortality, and other adverse events (AEs).

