#### Additional safety parameters

The GPs will be requested to document cardiovascular events (e.g., stroke, myocardial infarction) and mortality after 6 months (T_1_) and after 12 months (T_2_). The following safety parameters, if available, will be collected every 3 months by the GPs from the records:
Blood pressure level (mmHg)Heart rate (beats/min)Laboratory results: blood sugar (mg/dl), estimated glomerular filtration rate

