### Sample size

In a similar trial population, the mean rate of hospitalisations amounted to 0.38 per patient with a standard deviation of 0.75 during 6 months [44]. We assume that during an observation period of 12 months, the mean number of hospitalisations per patient will be 0.75 with a common standard deviation of 1.0, and we expect a decrease to a mean number of 0.5 in the intervention group. With a power of 80% and an alpha error of 0.05, we would need a sample size of 253 in each group (two-sided *t* test for equal variances) to detect the expected difference. For a cluster randomised intervention trial, the estimated sample size must be adjusted by the design effect. If an intra-cluster correlation of 0.05 is assumed and about five patients per GP are planned, the design effect would be 1.2 and the sample size would be 608 patients in 122 GP practices. With an estimated drop-out rate of 10% during the study period, 676 patients and 136 GPs will be needed in total.

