### Quality assurance and safety

Process flow and quality management of the study will be supervised quarterly by a scientific advisory board in repeated audits with study staff. The scientific advisory board will be involved in all decisions on important protocol modifications (e.g., changes to eligibility criteria, outcomes, analyses), followed by informing the relevant parties (investigators, trial participants, trial registries, journals, regulators).

During the intervention, each GP in the intervention group will be contacted at least twice by telephone to evaluate the progress of the study and to get information about potential harms for the patients regarding the safety parameters. Evidence suggests that serious AEs such as cardiovascular events (myocardial infarction, stroke) or death are not anticipated. Potential minor AEs are hyperglycaemia, elevated blood pressure, and recurrence of symptoms (e.g., dyspnoea, oedema) after stopping medication. The events will be reported to the data and safety monitoring board (DSMB) and relevant regulatory bodies as required, indicating expectedness, seriousness, severity, and causality.

To ensure high data quality, assessors (study nurses) will be trained on standardised patients regarding how to interview the patients and how to use the assessment tools. The personnel of the participating practices will not be involved in the collection of data.

Reliability training and checks will be performed before starting the study with the whole staff involved in interviewing and data collection. The quality assurance consists of procedures for prevention of insufficient data quality, detection of inaccurate or incomplete data, and action to improve data quality. In addition, the centres will regularly receive feedback by quality reports for data quality. External monitoring (e.g., for source data verification) would be desirable but too cost-intensive. As a solution, a random sample of paper crucial structure- and process-related factors will be compared with the data entries in the database.

For supervision of the study concerning the safety parameters and safety rules, a DSMB will be constituted. The DSMB will meet at least every 3 months starting and will evaluate the continuously collected safety parameters in a quarterly safety report. For this panel, at least two clinical and/or pharmacological researchers will be recruited who are not part of the COFRAIL project team or advisory board.

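### Other adverse events are requested from GPs only for patients who drop out, so symptom recurrence after stopping a drug has no scheduled collection in patients who stay

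*Protocol article*

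**What the plan says.** All references are to the Methods of the protocol article.

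- **Drop-outs** (Secondary outcomes, text below Table 1). The sentence opens "For patients who drop out of the study, the following parameters are requested by the GPs". It then names hospitalisations and cardiovascular events and closes with "mortality, and other adverse events (AEs".
- **All patients, events at 6 and 12 months** (Additional safety parameters). "The GPs will be requested to document cardiovascular events (e.g., stroke, myocardial infarction) and mortality after 6 months" and again after 12 months. Other AEs are not on this list.
- **All patients, further GP data.** Hospitalisations at 6 and 12 months (Primary outcome). New chronic diagnoses and medication schedules at 6 and 12 months (Measurements). Blood pressure, heart rate, blood sugar and eGFR every 3 months, if available (Additional safety parameters).
- **All patients, diary and nurse visits** (Measurements; Secondary outcomes). Falls, weight, emergency services and other health care use, depression, cognition, mobility, activities of daily living and quality of life.
- **Expected harms** (Quality assurance and safety). "Potential minor AEs are hyperglycaemia, elevated blood pressure, and recurrence of symptoms (e.g., dyspnoea, oedema) after stopping medication". Events are to go to the DSMB with expectedness, seriousness, severity and causality.

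**The concern.** The article states two GP harm lists, and which one applies depends on whether the patient has left the study. Three items match: hospitalisations, cardiovascular events and death. The fourth, other AEs, appears only for those who leave.

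The intervention encourages stopping drugs, and the primary hypothesis in the Background is framed as patient safety. A reader of the results will want to know whether symptoms returned more often in the intervention arm. That needs the event to be sought on the same basis in every randomised patient. Drop-out happens after randomisation in an open-label trial and may differ by arm. If collection depends on it, a difference in drop-out can look like a difference in harm, and a real difference among patients who stay can be missed.

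**Working it through.** **1. How many patients the request reaches.** The inputs are in Sample size: "the mean number of hospitalisations per patient will be 0.75 with a common standard deviation of 1.0". The intervention arm is assumed to fall to 0.5. The other inputs are 80% power, two-sided alpha 0.05, intra-cluster correlation 0.05, five patients per GP and 10% drop-out.

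- Difference 0.25, SD 1.0: the t-test calculation gives 252.1, so 253 per group.
- Design effect: 1 + (5 − 1) × 0.05 = 1.2.
- 253 × 1.2 = 303.6, so 304 per group and 608 in total; 608 / 5 = 121.6, so 122 practices.
- 608 / 0.9 = 675.6, so 676 patients; 122 / 0.9 = 135.6, so 136 GPs.

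This reproduces the plan: "676 patients and 136 GPs will be needed in total". Planned drop-outs are 676 × 0.10 = 67.6, about 68 (34 per arm). Planned completers are 676 × 0.90 = 608.4, about 608.

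**2. The named AEs against the scheduled sources for patients who stay.**

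| AE named in Quality assurance and safety | Scheduled source in patients who stay |
|---|---|
| Hyperglycaemia | Blood sugar, quarterly, if available |
| Elevated blood pressure | Blood pressure, quarterly, if available |
| Recurrence of symptoms (dyspnoea, oedema) | None, unless it leads to admission or other recorded care |

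The remaining sources do not fill the third row. The quarterly values contain no symptoms. Oedema that returns under a known diagnosis is not a new chronic diagnosis. The diary and nurse visits record care use and function, but neither the symptom nor its link to a stopped drug. The telephone contact about harms in Quality assurance and safety is described only for intervention-arm GPs and concerns the safety parameters, so it does not give equal collection across arms.

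**3. Illustration only.** The AE risks and unequal drop-out below are assumptions with no source in the article. They also assume that nothing is captured in patients who stay, which is the worst case, and the article plans no test of this kind. Power is for a two-sided comparison of two proportions (arcsine effect size, alpha 0.05), with n per arm divided by the design effect.

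| Assumed risk | All patients, 338 per arm, design effect 1.2 | Drop-outs, 34 per arm, design effect 1.2 | Drop-outs, 34 per arm, design effect 1 |
|---|---|---|---|
| 20% v 10% | 0.92 | 0.19 | 0.22 |
| 30% v 20% | 0.79 | 0.14 | 0.16 |

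The last column is the fairer one for drop-outs: 68 spread over 136 practices is about 0.5 per practice, so clustering hardly matters.

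If the true risk is 20% in both arms and drop-out is 12% v 8%, the captured counts are 338 × 0.12 × 0.20 = 8.1 and 338 × 0.08 × 0.20 = 5.4, a ratio of 1.5 with no true difference. At 13% v 7% the ratio is 0.13 / 0.07 = 1.9. These ratios arise when counts are compared per randomised patient. Dividing by the number of drop-outs removes them, but then describes a group selected after randomisation.

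**The case against.** The strongest reply is that the drop-out sentence is a fallback: it lists what is still sought from the GP once nurse visits and diaries stop. Naming other AEs there need not mean that they go unrecorded in everyone else. Quality assurance and safety says events will be reported to the DSMB and does not limit this to drop-outs, and the process evaluation includes telephone monitoring of physicians and patients. The article condenses a longer protocol, which may contain an AE form for all patients. Much of this stands, and it limits the point. It does not remove it: the article states both lists and they differ, no scheduled source is given for symptom recurrence in patients who stay, and the telephone monitoring is not said to ask about AEs.

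A reader might infer more than the text supports:

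- **That GPs report only cardiovascular events and death for patients who stay.** They also report hospitalisations, new chronic diagnoses and the quarterly values.
- **That most harms of stopping drugs go uncounted.** This cannot be computed from the article. Two of the three named minor AEs have a matching measurement, if available. Admissions, falls, emergency use and functional decline are recorded for everyone.
- **That AE counts will come mainly from drop-outs, or that the DSMB sees only that part.** The DSMB route is not restricted to drop-outs, and the DSMB's stated trigger is the hospitalisation rate, which is collected in all patients.

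The objection that the power and ratio figures rest on invented risks and zero capture is correct. They illustrate direction and scale and are not estimates for this trial.

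**Conclusion.** The point holds in a limited form. As written, GPs are asked for other AEs only for drop-outs, about 68 of 676 patients if the planned 10% holds. Non-cardiovascular AEs without admission, above all the symptom recurrence that the article itself expects, have no scheduled collection in the other 608 or so. Collection depends on an event after randomisation, so these AEs cannot be compared between arms per randomised patient.

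The primary endpoint is not affected, and neither are the harms recorded for everyone. The conclusion rests on the article alone. If the full protocol has an AE form for all patients, what remains is a misdescription in the article that still needs correcting.

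**What to change.** Reconcile the drop-out paragraph below Table 1, Additional safety parameters, and Quality assurance and safety. State one GP harm list that applies to every patient in both arms at months 6 and 12, whether or not the patient has dropped out: hospitalisations, cardiovascular events, mortality and other AEs, with a short tick list of the AEs that the article names. Make the drop-out list identical. Compare the proportion of patients with each AE by arm, with practice as a random effect. If the full protocol already has such a form, cite it and correct the article's lists.

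The cost is one more item on reports that GPs already make at 6 and 12 months: a few minutes per patient and some data entry, with no new staff or visits. It changes what is recorded and leaves treatment as it is.

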#### Additional safety parameters

The GPs will be requested to document cardiovascular events (e.g., stroke, myocardial infarction) and mortality after 6 months (T_1_) and after 12 months (T_2_). The following safety parameters, if available, will be collected every 3 months by the GPs from the records:
Blood pressure level (mmHg)Heart rate (beats/min)Laboratory results: blood sugar (mg/dl), estimated glomerular filtration rate

#### Additional health economic parameters

Intervention costs will be collected by the study centres and include personnel expenses, costs for the educational intervention (room and catering) material costs, printing costs, and postage related to manuals for physicians and information brochures for patientsCosts resulting from the consumption of health-related goods and services due to outpatient visits, visits to other health service providers, emergency admissions, hospital admissions, admissions to rehabilitation facilities, medical appliances, and support in households, and services of the long-term care insurance are estimated on the basis of patient questionnaires

### Sample size

In a similar trial population, the mean rate of hospitalisations amounted to 0.38 per patient with a standard deviation of 0.75 during 6 months [44]. We assume that during an observation period of 12 months, the mean number of hospitalisations per patient will be 0.75 with a common standard deviation of 1.0, and we expect a decrease to a mean number of 0.5 in the intervention group. With a power of 80% and an alpha error of 0.05, we would need a sample size of 253 in each group (two-sided *t* test for equal variances) to detect the expected difference. For a cluster randomised intervention trial, the estimated sample size must be adjusted by the design effect. If an intra-cluster correlation of 0.05 is assumed and about five patients per GP are planned, the design effect would be 1.2 and the sample size would be 608 patients in 122 GP practices. With an estimated drop-out rate of 10% during the study period, 676 patients and 136 GPs will be needed in total.

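### The 12-month SD of 1.0 is unexplained and lower than the protocol's own 6-month SD suggests; with an SD of about 1.06, power is about 75%, not 80%

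*Protocol article*

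**What the plan says.** All of this is in the sample size section of the protocol article. The source figures are: "In a similar trial population, the mean rate of hospitalisations amounted to 0.38 per patient with a standard deviation of 0.75 during 6 months". The planning assumption for 12 months is that "the mean number of hospitalisations per patient will be 0.75 with a common standard deviation of 1.0". The effect to be detected is worded as follows: "we expect a decrease to a mean number of 0.5 in the intervention group". For 80% power at a 5% alpha, the requirement before clustering is given thus: "we would need a sample size of 253 in each group (two-sided *t* test for equal variances"). After clustering, "the design effect would be 1.2 and the sample size would be 608 patients in 122 GP practices". After attrition, "With an estimated drop-out rate of 10% during the study period, 676 patients and 136 GPs will be needed in total". The section presents the 1.0 as an assumption. It gives neither a derivation from the 6-month SD nor a range of alternatives.

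**The concern.** The 12-month count for a patient is the sum of two 6-month counts. Doubling the mean from 0.38 to about 0.75 treats the second half-year like the first, so the variance should follow the same logic. It does not: 1.0 is less than the SD of two independent half-years, each with SD 0.75. The source figures also make a negative correlation between half-years an awkward assumption. Their variance (0.75² = 0.56) exceeds their mean (0.38), and when such overdispersion comes from lasting differences between patients the correlation is positive.

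The 253 per group, the 608 analysed and the 676 enrolled all rest on this SD, and they concern the primary endpoint. If the SD is too low, a non-significant result would be judged against a planned power that the trial did not have.

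**Working it through.** **Inputs, all from the sample size section.** 6-month mean 0.38 and SD 0.75 (variance 0.5625); 12-month means 0.75 and 0.50 (difference 0.25); common SD 1.0; two-sided alpha 0.05; power 80%; intra-cluster correlation 0.05 with five patients per GP; drop-out 10%. The correlation between a patient's two half-years, rho, is **not in the document** and is varied below.

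**Reproducing the plan.**
- Two-sided t test, difference 0.25, SD 1.0, 80% power: 252.1 per group, rounded up to 253.
- Design effect: 1 + (5 - 1) × 0.05 = 1.2.
- 253 × 1.2 = 303.6, so 304 per arm and 608 in total; 608 / 5 = 121.6, so 122 practices.
- 608 / 0.9 = 675.6, so 676 patients; 676 / 5 = 135.2, so 136 GPs.

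Every stated figure reproduces. The question is only the SD that goes in.

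**What the 6-month SD implies for 12 months.**
- Variance over 12 months = 2 × 0.5625 × (1 + rho) = 1.125 × (1 + rho).
- With rho = 0: SD = √1.125 = 1.06.
- For SD = 1.0: 1 + rho = 1 / 1.125 = 0.889, so rho = -0.11.
- Rounding does not remove the gap. With 0.745, the smallest SD that rounds to 0.75, the result is 0.745 × √2 = 1.05. Rescaling the variance to a mean of 0.75 instead of 2 × 0.38 = 0.76 also gives √(1.125 × 0.75 / 0.76) = 1.05. Power is 76% in both cases.

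**A negative binomial reading.** This assumes that all the overdispersion is stable between-patient difference.
- Dispersion k = (0.5625 - 0.38) / 0.38² = 1.264.
- Implied rho = (0.5625 - 0.38) / 0.5625 = 0.32.
- Control variance at 12 months: 0.75 + 1.264 × 0.75² = 1.461, SD 1.21.
- Intervention variance: 0.50 + 1.264 × 0.50² = 0.816, SD 0.90.
- Pooled SD: √((1.461 + 0.816) / 2) = 1.07.

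**A proportional-variance reading.** Half-years are uncorrelated, and the intervention variance falls in line with its mean.
- Control variance 1.125; intervention variance 1.125 × 0.50 / 0.75 = 0.75.
- Pooled SD: √((1.125 + 0.75) / 2) = √0.9375 = 0.97.
- With correlation rho the pooled variance is 0.9375 × (1 + rho). It stays at or below 1.0 up to rho = 1 / 0.9375 - 1 = 0.07.

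**Power.** Two-sided t test, difference 0.25, effective 304 / 1.2 = 253.3 per arm:

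| Assumption | SD used | Power |
|---|---|---|
| As stated | 1.00 | 80% |
| Common SD, rho = 0 | 1.06 | 75% |
| Common SD, rho = 0.1 | 1.11 | 71% |
| Common SD, rho = 0.2 | 1.16 | 68% |
| Negative binomial, separate variances (1.21 and 0.90) | 1.07 pooled | 75% |
| Negative binomial control SD in both arms | 1.21 | 64% |
| rho = 0, variance proportional to mean | 0.97 pooled | 83% |

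For scale, holding 80% would take 758 enrolled at SD 1.06 (284 per group; 682 after the design effect; 682 / 0.9) and 767 at SD 1.07 (287; 690; 690 / 0.9).

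**The case against.** The best defence is that nothing has been miscalculated. The 1.0 is labelled an assumption, it concerns a population only said to be similar to the source, and every later figure follows from it. This stands: the point is about an unexplained and somewhat favourable input, and a reader should not infer an arithmetic error.

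A second defence is that a single SD in an equal-variance t test with equal arms acts as a pooled SD. If the intervention arm varies less, a pooled 1.0 is compatible with a control SD of about 1.10 (variance proportional to mean: √(1.0 / 0.833) = 1.10). This also stands in part. On that reading power is about 83% with uncorrelated half-years and stays at or above 80% up to rho of about 0.07; at rho = 0.2 it is 75%. But it departs from the SD that the section states as common to both arms, and it needs nearly all the overdispersion to be short-lived.

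A reader might go the other way and infer that the figures prove a correlation of 0.32, a 12-month SD of 1.21 and hence 64% power. The document does not support this. One 6-month mean and SD cannot separate lasting differences between patients from readmissions bunched within one episode; bunching would leave rho near zero. And 64% puts the control-arm SD into both arms, whereas the negative binomial model that yields 1.21 gives 0.90 for the intervention arm, and so 75%.

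Finally, the statistical analyses section foresees adjustment for age, sex and co-morbidities. Covariates explaining about 11% of the variance (1 - 1 / 1.125) would offset the gap between 1.06 and 1.0. The sample size section claims no such gain, and nothing in the document shows that it would be reached.

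**Conclusion.** The point holds as a weakness in one planning input. The SD of 1.0 does not follow from the 6-month figure beside it and, for the control arm, requires a negative correlation between half-years that the protocol neither states nor supports. Under the plan's own common-SD t test, uncorrelated half-years give about 75% power, and the negative binomial with separate variances gives the same, so the central shortfall is about 5 percentage points. The full range is about 64% to 83%, depending on rho and on whether the intervention-arm variance falls with its mean; neither can be settled from the document. It would therefore be too strong to say that the trial certainly lacks 80% power. The stated 80% lacks support from the plan's own source, and the more natural readings put it lower. This should be fixed, with moderate confidence. It does not touch the endpoint, the analysis model or the conduct of the trial.

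**What to change.** Keep 676 patients and rewrite the paragraph in one of two ways:

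- **Justify 1.0**: give the evidence for a 12-month SD of 1.0, and say whether it is the SD in each arm or a pooled value.
- **Derive the SD**: obtain it from the 6-month figures, state the assumed correlation between half-years, and restate power for 0.75 versus 0.50 as about 75%.

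In either case, show power over the range of about 64% to 83% with the assumption behind each value: control SD of 1.21 in both arms (64%); SD 1.06 in both arms, or negative binomial with separate variances (75%); uncorrelated half-years with variance proportional to the mean (83%).

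The cost is one paragraph and a slightly less favourable stated power. No patients are added.

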### Randomisation

A cluster randomisation allocating the GP practices to the intervention or control group will be performed. To ensure a balance in sample size across groups over time, block randomisation of GP practices will be used. The randomisation procedure will be provided by the data management group at Hannover Medical School after enrolment of patients. The allocation sequence is computer-generated and concealed from researchers and interviewers. Randomisation lists will be kept closed. To assure concealment of allocation, no practice can start the intervention until recruitment of patients is complete and randomisation has been performed.

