### Study setting and participants

This study will be performed in a primary care setting in two areas of Germany (Düsseldorf and Rostock). At first, 136 GPs will be recruited. The GPs will be requested to enrol 676 frail elderly patients (average of 5 patients per GP) with polypharmacy living at home (Fig. 1). Patients are eligible to participate in the study if they meet all of the following criteria:
Positive screening of frailty in a short screening questionnaire answered by their GP using the Canadian Study of Health and Aging Clinical Frailty Scale [5]. Patients at levels 5–7 are eligible to participate in this trial.Aged 70 years or olderRegular intake of five or more different drugs per day (defined as polypharmacy)Care dependency (need for care assessed by the medical service of the German long-term care insurance) or comparable statusReceiving nursing care in the domestic environment, provided either by informal family carers alone or by professional ambulatory care services

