#### Primary outcome

The primary endpoint of the study is the number of hospitalisations per patient during the observation period of 12 months. This outcome does not include visits to an outpatient clinic or visits to an emergency unit without hospital admission. The hospitalisations will be documented by the participating GPs after 6 and 12 months and by the patients in their event diary. In case of disparity between the number of hospitalisations documented by GPs and patients, the study centre will be requested to validate the information on hospitalisation. If the information cannot be clarified, the higher value will be used for data analysis.

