### Data management

Data will be entered in the local centres via an Internet-based electronic data capture system which complies with US Food and Drug Administration requirements (21 CFR part 11) and the guidelines of good clinical practice. The data will be stored in a centralised Oracle database (Oracle Corp., Redwood City, CA, USA). The data will be transferred via 128-bit SSL (Secure Sockets Layer) encryption; there will be no local storage of data. The access to the database and webserver is controlled by two consecutive firewall systems. Data will be stored with a pseudonym. The members of the study teams will have access to the electronic data entry system according to a detailed concept of roles and rights. An audit trail ensures an automatic protocol of all data entries, changes, and deletions.

Contact details (e.g., address, telephone number) of the enrolled GPs and patients will be stored separately in electronic files at the study centres in Rostock and Düsseldorf with secure access for the study staff.

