### Data analysis

#### Statistical analyses

The analysis of the primary endpoint will be conducted according to the intention-to-treat principle. Sensitivity analyses will be performed on the basis of the per-protocol population (i.e., all patients who have finished the study without any protocol violations will be included in these analyses). Missing values will not be imputed *a priori*. To evaluate a possible bias due to values that are not randomly missing, sensitivity analyses based on multiple imputation will be performed.

Due to cluster randomisation, hierarchic multilevel models (mixed models) with GP practice as a random effect will be applied for the analyses of primary and secondary endpoints. Possible baseline imbalances and confounding variables (e.g., age, sex, co-morbidities) will be controlled by adjustment.

For the evaluation of the primary endpoint, a linear mixed model analysis of variance will be applied.

The analyses of the secondary endpoints will be performed by using linear mixed models or mixed logistic regression models (binary or ordinal), depending of the underlying distribution of the outcome variable.

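### Block randomisation of practices names no stratum for the two regions; stratifying by study centre and fitting a centre term would recover a little precision at almost no cost

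*Protocol article*

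**What the plan says.** Under Randomisation, the unit and the restriction are given: "A cluster randomisation allocating the GP practices to the intervention or control group will be performed", and "To ensure a balance in sample size across groups over time, block randomisation of GP practices will be used". Balance in sample size is the only stated purpose of the blocks. No stratum and no block size are named.

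On timing, the same section says: "The randomisation procedure will be provided by the data management group at Hannover Medical School after enrolment of patients". A practice's region is therefore known at allocation.

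The setting has two regions: "This study will be performed in a primary care setting in two areas of Germany (Düsseldorf and Rostock". Data management confirms a centre in each, since contact details "will be stored separately in electronic files at the study centres in Rostock and Düsseldorf".

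In the analysis, "hierarchic multilevel models (mixed models) with GP practice as a random effect will be applied", and "Possible baseline imbalances and confounding variables (e.g., age, sex, co-morbidities) will be controlled by adjustment". Region or centre is not among the examples, but the list is open. The Health economic evaluation section forms its ratios from differences in mean costs and mean outcomes between the arms, derived from cluster averages, and mentions no covariate adjustment.

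**The concern.** Region is a two-level factor, fixed before allocation, that may plausibly go with local hospital use and with costs. Blocks that ignore it balance the number of practices per arm but leave the regional mix of each arm to chance. If admission rates differ between regions, part of the variation in the arm contrast is regional variation that the design could have removed.

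What is at stake is some precision in the primary comparison. In the economic comparison, there is also a chance difference in regional mix that no stated adjustment takes out.

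**Working it through.** **Inputs from the protocol article (Sample size).** Means 0.75 and 0.5, so a difference of 0.25; SD 1.0; two-sided alpha 0.05; power 80%; intra-cluster correlation 0.05; five patients per GP; drop-out 10%; 676 patients and 136 GPs.

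**Assumptions, because the article gives no figure.** Regional split of practices 50:50 (60:40 and 70:30 also tried); 68 practices per arm; block size 4 or 8; regional difference D in admissions per patient-year of 0.2 (range 0.1 to 0.3).

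**1. The plan's own figure.**
- The two-sample t test needs 252.13, that is 253 per group.
- Design effect: 1 + (5 − 1) × 0.05 = 1.2.
- 2 × 253 × 1.2 = 607.2, that is 608 patients; 608/5 = 121.6, that is 122 practices.
- 608/0.9 = 675.6, that is 676 patients; 676/5 = 135.2, and 136 is the next whole number, and even.

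The stated sample size reproduces and does not depend on this point.

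**2. Chance imbalance in region.** At a 50:50 split, the number of practices from one region in one arm is hypergeometric:
- variance = 68 × 0.5 × 0.5 × 68/135 = 8.56, so SD = 2.93 practices;
- SD of the arm difference in regional share = 2 × 2.93/68 = 0.086, or 8.6 percentage points.

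Exact results by regional split:

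| Split | SD (points) | ≥10 points | ≥15 points | ≥20 points |
|---|---|---|---|---|
| 50:50 | 8.6 | 23.0% | 5.9% | 2.5% |
| 60:40 | 8.4 | 22.0% | 5.3% | 2.2% |
| 70:30 | 7.9 | 26.2% | 6.1% | 0.8% |

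Simulated blocks of 4 and 8 that ignore region (15,000 runs each) gave nearly the same figures.

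**3. What this costs in precision.**
- Planning SE = sqrt(2 × 1.2/304) = 0.0889. Power by the normal approximation: Φ(0.25/0.0889 − 1.96) = 80.3%.
- At D = 0.2, the regional contribution to the contrast has SD 0.2 × 0.086 = 0.0172, which is 0.0172²/0.0889² = 3.8% of the variance.
- With it removed, SE = sqrt(0.0889² − 0.0172²) = 0.0872 and power = 81.8%, a gain of 1.5 points.
- At D = 0.1 the power is 80.7% (gain 0.4 points). At D = 0.3 it is 83.7% (gain 3.3 points).

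A second route takes the regional variance, 0.25 × D², out of both the total variance and the intra-cluster correlation at 304 patients per arm. It gives 80.7%, 82.0% and 84.0% for D = 0.1, 0.2 and 0.3, so the size of the gain does not hang on the method. Both routes assume that the planning correlation of 0.05 includes the regional component.

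**4. What stratified blocks would do.** Separate blocks per region cap the arm difference within a region at half a block: 2 practices with blocks of 4 (2/68 = 2.9 points) or 4 practices with blocks of 8 (4/68 = 5.9 points). Without strata, the 95th percentile is 11 to 12 practices (16 to 18 points).

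**The case against.** **The article may only be silent.** It condenses a fuller protocol, and it speaks of randomisation lists in the plural, so separate lists per centre may already exist. This stands. It makes the remedy a one-sentence clarification in that case.

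**Chance imbalance is not bias.** A reader might infer that ignoring region biases the arm contrast. The documents do not support that. Unstratified randomisation is unbiased, and if the planning correlation covers all practices, the regional variance already lies inside the planning SE. This stands; only the loss of precision remains.

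**Differing endpoint validation.** When GP and patient reports of hospitalisation disagree, "the study centre will be requested to validate the information on hospitalisation". A reader might infer that the two centres validate differently and that regional imbalance carries this into the endpoint. Nothing in the text says so. The centre acts only on discordant counts, one common rule takes the higher value when a case cannot be clarified, and outcome assessors are described as blinded.

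**Unequal patient numbers.** Blocks of practices do not guarantee equal numbers of patients, so a stratum on practice size may seem called for. Each practice is asked for five patients. At an assumed coefficient of variation of 0.5 in practice size, the arm difference has SD sqrt(136) × 5 × 0.5 = 29 patients. Even at ±57, efficiency is 1 − (57/676)² = 0.993, which costs about 0.3 points of power. That stratum is not worth adding.

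**Adjustment is already possible.** The open covariate list permits a term for region but does not fix one, and the economic section states no adjustment. The objection stands in part.

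**Timing.** Recruitment opened on 15 March 2019 and was expected to end on 31 March 2020. Version 1.1 is dated 15 February 2020, 337 of 382 days (88%) into that period. Many practices may already have been allocated, so a change to the lists alone would achieve little. This stands, and it is why the fix needs the analysis term.

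**Conclusion.** The point holds as a minor improvement to the scheme as described. Region is known at allocation, no stratum is named, and nothing fixes an adjustment for it. Validity, type I error and the stated sample size are not in question.

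The gain in power is about 1.5 points at the assumed regional difference of 0.2, and 0.4 to 3.3 points over 0.1 to 0.3. It is realised only if centre is in the model. Stratifying without a centre term would leave the regional variance in the model-based SE and make the test slightly conservative. The regional difference and the regional split are assumptions with no figure in the article behind them, so confidence in the size is low.

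**What to change.** 1. Under Randomisation, state that blocks of practices are formed separately for the Düsseldorf and Rostock study centres. If this is already done, the sentence is a clarification. If not, it applies to practices not yet allocated.
2. Under Statistical analyses, name study centre as a prespecified fixed effect in the mixed models for the primary and secondary endpoints, beside the random effect for practice.
3. Under Health economic evaluation, state that the comparison of mean costs and outcomes is also adjusted for study centre.

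The cost is a second computer-generated list at the data management group and three sentences of text. It needs no extra patients or practices; 676 and 136 stand. If the lists are changed while the trial is running, the change should be documented with the date from which it applies, and it may need to go to the scientific advisory board, which is involved in decisions on important protocol modifications. If allocation is complete, items 2 and 3 alone remain useful.
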